### Qualitative analysis

Transcripts from FGDs and IDIs will be independently translated and transcribed. The results from the in-depth interviews and FGDs would be triangulated. Qualitative data management will be done using NVivo software, employing a combination of inductive-deductive approach. Inductive analysis will be done through reading the interview transcripts, and codes and subcodes will be generated. More precisely, thematic content analysis will be used to generate codes and sub-codes, themes and sub-themes. Results of the analysis will inform the design and development of the M0 + model, comprehensive wellbeing package. The overall framework of the intervention package and M0 + model will be finalized after the formative phase.

### Economic analysis

Microsoft Excel 2021, along with TreeAge software, is proposed for carrying out the proposed economic evaluation.

### Ethical considerations and declarations

#### Approval from the state health and education departments

Permission for conducting the study shall be obtained from the respective health and education/higher education departments of each state and union territory included in the study.

#### Ethics committee approval

The research protocol has been approved by the eight institutional ethics committees situated at Andaman & Nicobar Islands (Andaman and Nicobar Islands Institute of Medical Sciences, Sri Vijaya Puram), Arunachal Pradesh (Rajiv Gandhi University, Papum Pare), Assam [All India Institute of Medical Sciences (AIIMS), Guwahati], Karnataka [National Institute of Mental Health and Neuro Sciences (NIMHANS), Bengaluru], Kerala (Government Medical College, Kollam), Maharashtra [Tata Institute of Social Sciences (TISS), Mumbai], New Delhi [Institute of Health Behaviour and Allied Sciences (IHBAS)], and Rajasthan [All India Institute of Medical Sciences (AIIMS), Jodhpur]. The research will be carried out in alignment with the principles of the Helsinki Declaration and after obtaining clearance from the Institutional Ethics Committee. Important protocol modifications (e.g., changes to eligibility criteria, outcomes, and analyses) to relevant parties (e.g., investigators, the Institutional Ethics Committee, trial registries, journals, and regulators) will be communicated. Written informed consent will be obtained from the participants. Protocol amendments will be submitted to the respective IECs.

All self-help and training resources/material created on mental health and well-being will be checked for quality and accuracy. The material will be strengths-based, non-stigmatizing and will be evidence informed. All self-help and training resources/material and data collection tools will be translated in local languages to ensure access/reach and the translations will be reviewed for quality. In addition, the master trainers and team members conducting training for the program will be duly trained and will ensure safety of all trainee participants. The research team will also be trained and oriented to research ethics.

To safeguard the rights and interests, along with seeking permission from school leaders, an assent from the adolescent participants along with an informed consent will be obtained from their parents/guardians. For students in residential schools, permission will be sought from the warden or guardian, as it may not always be possible to reach the parents. All participants will be informed that the information they share will remain confidential and will not be shared with other students or stakeholders, with the exception of harm to themselves or others. Since the study will ascertain data about stress levels and self-harm, participants will be asked to share on the PIS/PICF the information of a trusted adult/parent who can be contacted for support if they have high distress or are at high risk for self-harm.

#### Management of adverse events

In instances where participants reports high distress or risk of harm on the study tools, the research team will inform the gatekeeper of the respective institute to assess risk and as needed follow the protocol of high-risk situations and contact the trusted adult (for participants above 18 years) or parents (for participants below 18 years) as per limits of confidentiality. The consent for this will be sought from the students at the start through the PIS and PICF and this will be clearly mentioned in the same. The team will not inquire into or insist on participants sharing any emotionally difficult material or making any personal disclosures. The research team will be trained to identify and provide immediate psychosocial support to participants expressing any emotional distress during the program. If additional support is deemed necessary, the contact details of trained counselors or helpline numbers offering subsidized/free psychotherapeutic services shall be provided to the participants and their families.

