Reach: The number and proportion of individuals who are exposed to and participate in a program	—	Number and proportion of youth champs who engage in the program The number/proportion of youth beneficiaries who are reached/exposed to the program	Number and proportion of gatekeepers who engage in the program	Responses from the target population (youth beneficiaries) regarding exposure to, participation in the intervention programs conducted, and awareness about nature of resources made accessible and how to access the same
Appropriateness: Perceived fit, relevance to address a particular issue	–	Appropriateness of campaign -based intervention	Appropriateness of campaign-based intervention and gatekeeper intervention	Intervention Appropriateness Measure (IAM)*
Feasibility: The extent to which the program can be successfully carried out within a given setting	Overall feasibility of implementing intervention package at institutes	Feasibility of campaign -based intervention	Feasibility of campaign -based intervention and gatekeeper intervention	Feasibility of Intervention measure (FIM)* (Youth champs, gatekeepers) Interviews with leaders and coordinators at institutes Field observation notes
Fidelity: Degree to which the intervention was implemented as planned	–	Sampling of universal campaigns conducted (direct observations/records of the same)	Examination of data on gatekeeper behaviors measure	Observations, Gatekeeper behaviors data and Other relevant logs/records, e.g., referrals made following identification of high distress
Acceptability: Perception of stakeholders that a given intervention is agreeable	Leaders/Coordinators’ Views	Rated by Youth champs and sample of beneficiaries: Universal programs/Campaigns	Rated by gatekeepers about gatekeeping intervention	Acceptability of Intervention measure (AIM)* plus additional feedback items Interviews with leaders and coordinators (Regarding overall package)
Implementation cost				Pragmatic approach by Cidav et al. (62) **

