Effectiveness	Mean score of: Depressive symptoms-PHQ-9 Perceived stress-PSS10 Help seeking inclination-GHSQ Help-Seeking Behavior	Proportion of youth champions who were approached by distressed students for help Proportion of distressed students referred by youth champions to gatekeepers or school leaders Proportion of students who accessed self - help modules	Proportion of gatekeepers who were approached by distressed students for help Proportion of distressed students referred by gatekeepers	Administrative data and records self-reported/log books maintained by gatekeepers and youth champions
Sustainability: Extent to which the intervention is maintained/institutionalized	Key informant interviews by district authorities and leaders			Testimonials by gatekeepers and youth champions and youth beneficiaries if possible

**Described in detail under statistical analysis heading.

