### Study outcomes

#### Primary outcomes

The present study focuses on the following primary outcomes:

Reduction in suicide risk factors: This is measured by a decrease in perceived stress levels and depressive symptoms among students in educational institutions using validated scales.Improvement in help-seeking behavior: This is measured by a rise in the proportion of individuals engaging with services/aid for mental health.

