### Data collection

Data collection will be conducted in a retrospective manner to document the activities undertaken and their frequency across three phases: the pre-implementation phase (e.g., initial meetings, development of training manuals), the refinement phase (pilot testing and adaptation of the intervention), and the implementation and sustenance phase (trainings, meetings, and other activities carried out as per the refined model framework). The activities will be cost separately for each type of educational institution, considering the heterogeneity in functioning and resource use.

For each category of activity, the corresponding quantity of resources for which financial allocations were made will be assessed through stakeholder interviews with implementation teams and a review of relevant records. Resource prices will be obtained from records on actual financial allocations made, supplemented by information from personnel interviews, administrative documents or standard cost databases. For activities performed by the research team to support the implementation of the strategies, shadow pricing will be applied to document the full implementation costs to facilitate potential scale-up. In contrast, activities conducted exclusively for research and evaluation purposes will be excluded from the costing analysis. Likewise, the opportunity cost of undertaking implementation activities will not be considered.

In parallel, the evaluation will capture the impact of the suicide risk reduction strategy on healthcare-seeking behaviors, specifically by measuring the change in the number of students accessing health services following referral by educational institution staff at three time points: baseline (pre-intervention), midline (6 months), and endline (12 months). The incremental costs of outpatient consultations resulting from these referrals will also be incorporated into the final cost of the implementation package.

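### Gatekeeper alerts set off by the study's own questionnaires are not separated from the model's own contacts in the referral, fidelity and help-seeking measures

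*Protocol article*

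**What the plan says.** The alert is described under Management of adverse events. If a student's answers signal serious distress or danger, "the research team will inform the gatekeeper of the respective institute to assess risk and as needed follow the protocol of high-risk situations". The notice to the gatekeeper carries no condition. What comes after the gatekeeper's assessment does, including any call to a trusted adult, or to a parent for those under 18. The consent text likewise speaks of "a trusted adult/parent who can be contacted for support if they have high distress or are at high risk for self-harm".

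Table 1 (Intervention components) gives three routes to a gatekeeper: the student comes forward, the gatekeeper takes the initiative, or a youth champion refers. An alert from the research team is not one of them, and no row of the table is a screening component. The sentence that introduces the table, however, names risk-assessment tools among the components.

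The measures that could pick up alert-driven contacts are:
- Effectiveness, Table 4: "Proportion of distressed students referred by gatekeepers".
- Fidelity, Table 4: gatekeeper behaviour data and "Other relevant logs/records, e.g., referrals made following identification of high distress".
- Primary outcome, help-seeking: "This is measured by a rise in the proportion of individuals engaging with services/aid for mental health".
- Cost analysis, Data collection: the change in the number of students using health services after referral by institution staff, with the resulting outpatient costs added to the package cost.

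None of these is divided by what prompted the contact.

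**The concern.** The survey that measures the outcome also sets off an action that the outcome measures can register. A gatekeeper told by the research team about a distressed student may approach that student, refer, and log the referral. The student may then report contact with a teacher, counsellor or helpline, which are among the help sources listed for the help-seeking questionnaire.

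Only assessed students can be flagged in this way, and the research team collects the data (Phase 2). If the model is later rolled out without the study questionnaires, this source of contacts disappears. Credit given to the model for such contacts would carry over into the scale-up advice. Phase 1 collects the same kinds of outcome to choose the refined model, so that choice could be affected too.

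**Working it through.** The plan gives no figure for this point. The check is therefore a trace through the text, followed by an illustration of size.

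**Trace**
1. Trigger: answers on the study's own tools (Management of adverse events).
2. Who acts: the institute's gatekeeper. Table 1 defines gatekeepers as teachers, wardens and counsellors, the same people whose behaviour and referrals Table 4 counts.
3. Timing: youth and gatekeeper tools are first used before training (Assessment time-points). Help recalled at T1 therefore largely predates any alert, while later rounds follow one or more screens.
4. Comparator: the sample size section plans a change within a group from T1 to T4, and no control group is described. Nothing in the design subtracts the alert's contribution.
5. Separation: no item, log or indicator in the article asks what prompted a contact. The gatekeeper item on youth approached does not ask whether the study team prompted it. The limitations name Hawthorne effect, recall and social desirability, but not this pathway.

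Steps 1 to 5 give the bias a direction: upward after baseline for help-seeking, and for referral and fidelity records in so far as alerts are acted on.

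**Illustration of size**

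Inputs from the sample size section: PHQ-9 baseline mean 8.5, SD 5.0, 400 students per stratum. Assumed: a normal shape with continuity correction, and an alert threshold at the lower edge of one of the two highest PHQ-9 bands described in the article.
- Score 15 or more: 1 − Φ((14.5 − 8.5)/5) = 1 − Φ(1.2) = 0.115; 400 × 0.115 = 46 students.
- Score 20 or more: 1 − Φ((19.5 − 8.5)/5) = 1 − Φ(2.2) = 0.014; 400 × 0.014 ≈ 6 students.

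Truncated-normal, gamma and beta-binomial shapes with the same mean and SD give 11.8% to 13.2% and 1.4% to 3.4%. Alerts from the PSS-10 or from other reports of risk would add to these.

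The effect on the help-seeking proportion is the share flagged times the share of those who engage only because of the alert. The second factor is unknown, so a range is assumed:

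| Share engaging only because of the alert | 11.5% flagged | 1.4% flagged |
|---|---|---|
| 25% | 2.9 points | 0.35 points |
| 50% | 5.8 points | 0.7 points |
| 100% | 11.5 points | 1.4 points |

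These are per assessment round, in the surveyed sample, with no model effect at all.

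**The case against.** The strongest reply is that screening may be part of the model. The sentence introducing Table 1 names assessment tools among the components, and the Discussion lists early identification of risk as a focus. On that reading, counting these contacts is legitimate. But Table 1 has no such component and the research team runs the assessments, so the article supports neither reading clearly.

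A second reply is that no passage says alert-driven contacts will be counted, and that indicator definitions belong in fuller documents. It is true that the counting is inferred from definitions that make no distinction. It still matters now: the prompt must be noted when the contact happens, the logs cannot be reliably split later, and recruitment is under way.

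Third, the measures are not all equally exposed. The referral measure is a proportion of distressed students, so alerts can enter numerator and denominator, and a rise is not automatic. Being approached by a gatekeeper is not plainly help sought by the student. The gatekeeper behaviour items look back 3 months, so they capture a previous round's alerts more readily at the 3-month intervals in the text than at the T2 to T4 times in Table 3. Institute-wide logs dilute the effect. These points narrow the concern but do not remove it.

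A reader might also infer three stronger things, which the documents do not support:
- That families are contacted for every distressed student. That step is conditional in both passages that mention it.
- That the costing contradicts itself. The rule that "activities conducted exclusively for research and evaluation purposes will be excluded from the costing analysis" does not reach an outpatient consultation after a staff referral, which is care.
- That alerts or learned under-reporting explain a fall of several PHQ-9 points. No figure supports this, and disclosure is explained at consent, so it applies at T1 too. Flagged students would also fall by regression to the mean. With the plan's correlation of 0.5, those at 15 or more average 8.5 + 5 × 0.1942/0.1151 = 16.9, and 8.5 + 0.5 × 8.4 = 12.7 is expected later, a fall of 4.2 with no cause at all.

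**Conclusion.** The point holds in a limited form. The study's questionnaires create an unconditional notice to the gatekeeper. The outcome, fidelity and service-use measures do not distinguish contacts that arise from it, and the single-group design with a pre-training baseline turns that into a possible upward bias.

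The size cannot be fixed from the article. It could be under 1 percentage point of help-seeking or more than 5, depending on the unstated alert threshold and on how many flagged students engage only because of the alert. Both are assumptions here. The PHQ-9 and PSS-10 results are not shown to be affected. This is a cheap improvement to recording and reporting, not a flaw that undoes the study, and it raises no objection to the safety pathway.

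**What to change.** Leave the safety pathway exactly as it is. Then:
1. Reconcile the introductory sentence of Intervention components with Table 1, stating whether screening by questionnaire belongs to the model. If it does, list it and cost it as a component.
2. Add one field to REDCap and to the gatekeeper and youth-champion logs: was this contact or referral prompted by a study assessment, and at which round?
3. Report the Table 4 referral, gatekeeper-behaviour and fidelity measures, and actual help-seeking, with and without alert-prompted contacts. Where the measure is a proportion, remove them from numerator and denominator alike. Present the figures as a pair, since some flagged students would have been reached anyway.
4. Show the cost of consultations that followed alerts on a separate line. Do not delete it: those students' score changes stay in the cost per unit reduction, so deletion would make the package look cheaper than it is.
5. Do not tabulate PHQ-9 or PSS-10 change by earlier alert. That selects on the outcome and would mainly display regression to the mean.

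The cost is a small recording burden and a few extra table lines. Referral and help-seeking figures may look less favourable.

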## Discussion

The protocol outlines a comprehensive, implementation model for suicide prevention among students at educational institutes across selected states in the country. The study focuses on mental health promotion, early risk identification and establishment of structured referral pathways. Varied contributing factors spanning academic stress, family issues, interpersonal conflicts, anxiety, performance pressure besides others, contribute to suicide being a leading cause of death among individuals aged 15–29 years in India. Prior literature emphasizes comorbid psychiatric conditions significantly heighten the risk of suicide among youth, underscoring the need for multi-component interventions to address overlapping mental health concerns in educational institutes (7, 61) his study aims at addressing critical gaps in the current prevention mechanisms by integrating an evidence-based capacity building for gatekeepers, youth volunteers and linking individuals to professional care within educational systems.

This multi-sectoral implementation model is grounded in the WHO’s recommendation for youth suicide prevention. The training modules for leaders, gatekeepers and peer supporters are designed to improve early identification and appropriate response toward an individual at potential risk of suicide.

Anticipated challenges include varying levels of institutional readiness, stigma and prejudice around help-seeking and need for sustained engagement from educational authorities. Mitigation strategies include iterative model refinement phases, continuous sensitization activities and collaboration with state education and health departments. Implemented in eight states across the country, the results generated in the study would be prima-facie for policy framing and contribute in value addition and refinement of the national mental health policy and other state initiated measures for mental wellbeing of students.

Furthermore, outputs from different phases of the study will be reported separately to capture evolution of intervention and facilitate scalability. The protocol holds potential to inform a sustainable, replicable model for youth suicide prevention and promotion of mental wellbeing in low-and-middle income countries like India.

The current study has certain limitations including implementation research limited to certain states and districts; in some states it may be difficult to achieve targeted sample size due to heterogeneity in the infrastructure, staff and practices and possible differences in participant profiles across sites; however, this will increase the generalizability of our findings. In addition, results may not be attributed to individual model components (some approaches may be ineffective and will be dropped, while others with success may be preserved, sometimes with modifications). The Hawthorne effect and recall bias in reporting compliance, as well as social desirability bias (within proximity of implementation support and program learning teams) are possible limitations. Furthermore, it may not be feasible to examine longer term effects in terms of sustainability once the final model is in place as the total project duration is limited to 3 years and model iterations are planned as part of implementation research in the initial phase.

The dissemination plans include publishing the results after appropriate approval, including professional, public and private avenues such as academic journals, seminars, conferences and workshops. After the data collection, we intend to publish multiple articles based on the different phases of the study.

## Conclusion

The existing protocol is a multi-site intervention implemented at educational institutes in selected states of India. The objective is to develop an implementation model for reduction of suicidal behavior specifically, aimed at reduction of levels of perceived stress and depressive symptoms while enhancing help seeking behavior among students and optimize the model through repetitive cycles of implementation, evaluation and refinement. The study will measure the cost implications of incorporating the mental health and wellbeing improvement intervention package within the education and healthcare system.

